##### Data storage, confidentiality, and retention

All original study data, including signed informed consent forms, paper CRFs, original electronic anesthesia records, archived ultrasound images, pulmonary function test reports, follow-up records, and adverse event documentation, are archived in a dedicated locked file cabinet in the study center, with access restricted only to authorized study personnel. Electronic data in the ResMan system are encrypted and stored on the platform’s dedicated server, with regular automatic backups to ensure data security and prevent data loss.

All study data are de-identified, with the subject’s personal identifiable information replaced by a unique study ID, to protect the subject’s privacy in strict accordance with the Personal Information Protection Law of the People’s Republic of China and relevant international privacy regulations. All study data will be retained for at least 5 years after the completion of the study and the publication of the study results, in compliance with GCP regulations and the requirements of the institutional ethics committee.

##### Data quality assurance and monitoring

A full-process data quality control system is established throughout the study. Before the formal initiation of the trial, unified standardized training is conducted for all study personnel involved in data collection, including the outcome assessor, anesthesia management team, PACU nursing staff, and data management team, to ensure that all personnel fully understand the study protocol, eCRF filling specifications, and data collection standards in the ResMan system.

Regular on-site monitoring is performed by an independent clinical research associate (CRA) who is not involved in the study implementation, at least once a month during the subject enrollment period. The monitoring content includes the compliance of the study implementation with the protocol, the integrity and authenticity of the eCRF in the ResMan system, the consistency between the eCRF and the source data, the management of the randomization list and study drugs, and the recording and reporting of adverse events. All monitoring findings, corrective actions, and follow-up results are fully documented in the monitoring report. All protocol violations and deviations are recorded, classified, and reported to the institutional ethics committee in a timely manner, with the impact on the study results evaluated and documented.

### Data collection

All study data are collected at pre-specified time points in accordance with the study protocol, with the specific collection content as follows:

*Screening and baseline data*: Subject demographic information (age, gender, height, weight, BMI), ASA physical status classification, preoperative comorbidities (hypertension, diabetes, cardiovascular disease, chronic pulmonary disease, etc.), past medical history (ipsilateral shoulder or cervical surgery history, chronic pain history, allergy history), preoperative vital signs (heart rate, blood pressure, SpO₂), preoperative laboratory test results (hemoglobin, platelet count, coagulation function, liver and kidney function), and preoperative pulmonary function and diaphragmatic excursion baseline measurements (FEV1, FVC, FEV1/FVC ratio, ipsilateral diaphragmatic excursion value).*Intraoperative data*: general anesthesia related data (induction and maintenance drug dosage, anesthesia duration, surgery duration, laryngeal mask airway extubation time, emergence time), intraoperative hemodynamic parameters, total dosage of intraoperative analgesic and vasoactive drugs, intraoperative fluid balance (infusion volume, blood loss, urine output), and any protocol deviations or adverse events during the operation.*Post-anesthesia care unit (PACU) data*: Pre-rescue analgesia NRS pain score assessed immediately after the patient regains full consciousness from general anesthesia (before rescue analgesia in PACU), postoperative diaphragmatic excursion and pulmonary function measurements, PACU stay duration, rescue analgesia administration details, emergence and recovery related indicators, and any adverse events during the PACU stay.*Safety and compliance data*: Detailed records of all perioperative adverse events and serious adverse events, including onset time, severity, causal relationship with the study intervention, treatment measures, and final outcome; detailed records of subject withdrawal, loss to follow-up, and protocol deviations, including specific reasons and corresponding handling measures.

### Outcomes

#### Primary outcomes

This trial adopts a dual co-primary endpoint design to simultaneously verify the non-inferiority of analgesic efficacy and the superiority of diaphragmatic safety of the 2 mL local anesthetic regimen:

1 Pre-rescue analgesia NRS pain score assessed immediately after the patient regains full consciousness in the PACU

*Evaluation tool*: 11-point NRS (0 = no pain, 10 = the worst imaginable pain)*Evaluation time*: Immediately after full consciousness and ability to accurately report discomfort, strictly before any rescue analgesia administration*Study objective*: To test the non-inferiority of 2 mL 0.375% ropivacaine compared with 5 mL 0.375% ropivacaine in postoperative analgesic efficacy, with a predefined non-inferiority margin of 1 point on the NRS scale.

2 Incidence of ipsilateral hemidiaphragmatic paralysis (HDP) assessed before discharge from the PACU

*Definition*: Complete paresis: A reduction in diaphragmatic movement of more than 75%, no movement, or paradoxical movement. Partial paresis: A reduction in diaphragmatic movement between 25 and 75%.*Evaluation tool*: Ultrasound measurement of diaphragmatic excursion via the anterior subcostal approach (M-mode)*Evaluation time*: Strictly before discharge from the PACU, performed by the same blinded investigator who conducted the baseline measurements*Study objective*: To test the superiority of 2 mL 0.375% ropivacaine compared with 5 mL 0.375% ropivacaine in reducing the risk of HDP.

#### Secondary outcomes

1 Diaphragmatic function parameters

Absolute value of ipsilateral diaphragmatic excursion before discharge from the PACUAbsolute and percentage changes in ipsilateral diaphragmatic excursion from preoperative baseline to PACU discharge

2 Pulmonary function parameters

Absolute values of forced expiratory volume in 1 s (FEV1) and forced vital capacity (FVC) before discharge from the PACUAbsolute and percentage changes in FEV1 and FVC from preoperative baseline to PACU discharge

3 Upper extremity sensorimotor block characteristics

Sensory block scores of the radial, median, ulnar, musculocutaneous and axillary nerves before discharge from the PACU (0 = no block; 1 = analgesia, intact touch sensation but absent cold sensation; 2 = anesthesia, absent touch sensation)Motor block scores of the radial, median, ulnar, musculocutaneous and axillary nerves before discharge from the PACU (0 = normal movement; 1 = partial paralysis; 2 = complete paralysis)

4 Perioperative analgesic drug consumption

Total intraoperative sufentanil dosageTotal sufentanil dosage administered for rescue analgesia in the PACU

5 Recovery-related indicators

Total time interval from completion of nerve block to PACU dischargeSurgical durationPACU stay durationPostoperative hospital length of stay

6 Safety indicators

Incidence of all perioperative adverse events, including nausea, vomiting, pruritus, hypotension, bradycardia, local anesthetic toxicity, nerve injury, Horner syndrome, hoarseness and dyspneaIncidence of serious adverse events related to the study intervention, including severe respiratory distress, anaphylactic reaction and permanent neurological deficitIncidence of protocol deviations and subject withdrawal/loss to follow-up, with detailed documentation of specific reasons

#### Sample size calculation

The sample size calculation is based on the dual co-primary endpoints of this trial: the non-inferiority of analgesic efficacy (PACU pre-rescue NRS pain score) and the superiority of diaphragmatic safety (incidence of hemidiaphragmatic paralysis, HDP). All calculations are performed using PASS 15.0.5 software (NCSS, LLC, Kaysville, UT, USA) with a one-sided significance level (*α*) of 0.025 and a statistical power (1-*β*) of 0.80, consistent with the design of randomized non-inferiority trials in anesthesiology.

##### Sample size calculation based on analgesic efficacy non-inferiority endpoint

The primary non-inferiority endpoint is the difference in pre-rescue NRS pain scores between the 2 mL group and the 5 mL group immediately after full consciousness in the PACU. The predefined non-inferiority margin is 1 point on the 11-point NRS scale, which is widely accepted as the minimal clinically important difference (MCID) for postoperative pain assessment in orthopedic surgery. This margin was also used in previous similar trials comparing different volumes of local anesthetic for brachial plexus block.

Based on the results of our preliminary study (*n* = 11) and previously published literature, the standard deviation (SD) of NRS pain scores in patients undergoing arthroscopic shoulder surgery with upper trunk brachial plexus block is estimated to be 1.6. Using the two-sample Z-test for non-inferiority with pooled variance, the required sample size per group is calculated as follows:
$$n=\frac{2{\left(Z_{1-\alpha }+Z_{1-\beta }\right)}^{2}\sigma^{2}}{\delta^{2}}$$
Where 
$Z_{1-\alpha }=1.96$
 (one-sided *α* = 0.025), 
$Z_{1-\beta }=0.84$
 (power = 0.80), 
σ=1.6
, and 
δ=1
 (non-inferiority margin). Substituting the values yields a required sample size of 40 patients per group.

##### Sample size calculation based on HDP incidence superiority endpoint

The primary superiority endpoint is the difference in the incidence of ipsilateral HDP between the two groups. Based on the study by Zhang et al. (27), the incidence of HDP in patients receiving 5 mL 0.375% ropivacaine via subparaneural injection at the upper trunk bifurcation is 16.67%. Our preliminary study (n = 11) showed that no HDP occurred in patients receiving 2 mL 0.375% ropivacaine via the same technique, leading to our core hypothesis that the HDP incidence of the 2 mL regimen is infinitely close to 0.

However, the PASS 15.0.5 software does not allow setting the group proportion to 0 in the two-sample Z-test for superiority of proportions. To accurately reflect our preliminary findings and satisfy the software’s calculation requirements, we set the HDP incidence in the 2 mL group to an extremely small value of 1 × 10^−20^, which is mathematically indistinguishable from 0 for all practical clinical purposes.

Using the two-sample Z-test for superiority of proportions with pooled variance, the required sample size per group is calculated as follows:
$$n=\frac{{\left(Z_{1-\alpha }+Z_{1-\beta }\right)}^{2}(p_{1}(1-p_{1})+p_{2}(1-p_{2}))}{{\left(p_{1}-p_{2}\right)}^{2}}$$
Where 
$p_{1}=0.166667$
 (HDP incidence in the 5 mL group), 
$p_{2}=1\times 10^{-20}$
 (estimated HDP incidence in the 2 mL group), 
$Z_{1-\alpha }=1.96$
, and 
$Z_{1-\beta }=0.84$
. Substituting the values yields a required sample size of 40 patients per group.

##### Final sample size determination

The larger sample size requirement from the two co-primary endpoints is 40 patients per group. To account for potential subject withdrawal or loss to follow-up during the trial, we will recruit additional subjects to ensure that the final ITT analysis set includes at least 40 patients per group. Considering a conservative dropout rate of 20%, we will recruit a total of 100 patients (50 patients per group) for this trial.

Any subjects who withdraw from the study before completing all primary outcome assessments will be replaced by newly enrolled subjects in strict sequential order to maintain the integrity of the randomization sequence and ensure the required statistical power.

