##### Multiplicity adjustment

No multiplicity adjustment will be performed for the two co-primary endpoints, as they address distinct and independent research questions (analgesic efficacy vs. diaphragmatic safety), and both must be statistically significant to declare the overall success of the trial.All secondary outcomes are exploratory in nature and will not undergo multiplicity adjustment. Results will be presented with point estimates and 95% CIs, and *p* values will be interpreted descriptively rather than as definitive hypothesis tests.

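### The 80% power at 40 per group is per endpoint; for the trial's own rule that both co-primaries must succeed, power at 40 is about 0.64 to 0.72

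*Protocol article*

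**What the plan says.** The section Sample size calculation sets a "one-sided significance level (*α*) of 0.025" and a "statistical power (1-*β*) of 0.80", and the two subsections that follow apply these to one endpoint each.

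- **Pain score (non-inferiority).** "The predefined non-inferiority margin is 1 point on the 11-point NRS scale", and the SD "is estimated to be 1.6". The formula has no term for a true difference, so it assumes 0. "Substituting the values yields a required sample size of 40 patients per group".
- **HDP (superiority).** The 5 mL rate is 16.67%, from a published study. For the other arm, "we set the HDP incidence in the 2 mL group to an extremely small value", namely 1e-20, because none of 11 pilot patients had HDP and the software does not accept 0. The text names a pooled variance, the printed formula is unpooled, and the result is again 40.
- **Final number.** "The larger sample size requirement from the two co-primary endpoints is 40 patients per group". A 20% dropout rate takes this to 50 per group, 100 in total. Handling of study withdrawals adds that, with this allowance, the study's power is kept despite the expected withdrawals.
- **Success rule.** Under Multiplicity adjustment, no alpha adjustment is made, partly because "both must be statistically significant to declare the overall success of the trial".

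**The concern.** Requiring both endpoints removes the need to adjust alpha, but it adds up the chances of missing. A trial with 80% power on each of two endpoints has less than 80% power to win on both, unless the two results almost always succeed and fail together. The protocol reports no joint power. It carries the per-endpoint figure forward as the power of the design and says that it survives 20% dropout, yet 40 evaluable per group is where the joint shortfall is largest.

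The HDP calculation also examines only the most favourable 2 mL rate, with 0 events in 11 patients as support. If the trial missed on one endpoint, a reader who believed it had 80% power for overall success would give that miss more weight against 2 mL than the design justifies.

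**Working it through.** **Inputs.** One-sided alpha 0.025, power 0.80, margin 1, SD 1.6, HDP 16.67% against about 0, 40 per group, 20% dropout (sample-size sections); equal-variance t-test and two-sample Z-test (Analysis of primary outcomes); both endpoints required (Multiplicity adjustment). Independence of the endpoints and any non-zero 2 mL rate are assumptions of this review.

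**1. The plan's own figures.**
- Pain score: 2 × (1.96 + 0.84)² × 1.6² / 1² = 40.14. Rounded up this is 41; the plan states 40.
- HDP, printed (unpooled) formula: 7.84 × (0.166667 × 0.833333) / 0.166667² = 39.2, so 40, as stated.
- HDP, pooled as the text says, mean rate 0.0833: [1.96 × √(2 × 0.0833 × 0.9167) + 0.84 × √0.1389]² / 0.02778 = 41.9, so 42.
- Dropout: 40 / 0.8 = 50.

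The stated 40 is reproduced to within rounding.

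**2. Power per endpoint at 40 per group.**
- Pain score: standard error 1.6 × √(2/40) = 0.358; 1/0.358 = 2.795; Φ(2.795 − 1.96) = 0.798. With the planned t-test (noncentral t), 0.788.
- HDP, printed formula: standard error √(0.1389/40) = 0.0589; 0.1667/0.0589 = 2.828; Φ(2.828 − 1.96) = 0.807.
- HDP, exact enumeration of the Z-test: with no 2 mL events, 4 events in the 5 mL arm are enough, and the chance of at least 4 is 0.919.

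**3. Joint power on the plan's own inputs, endpoints independent.**
- 40 per group: 0.798 × 0.807 = 0.64 (printed formulas); 0.788 × 0.919 = 0.72 (exact).
- 50 per group: 0.878 × 0.885 = 0.78; 0.872 × 0.976 = 0.85.
- Any correlation, 40 per group, exact: at least 0.788 + 0.919 − 1 = 0.71 and at most 0.788. At 40 per group, 80% cannot be reached.

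**4. Dependence on the 2 mL rate.** With 0/11, the exact one-sided 95% upper limit is 1 − 0.05^(1/11) = 23.8%. The non-zero rates below are assumed for illustration, and all lie well inside that limit.

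| True 2 mL HDP rate | HDP power, 40 / 50 | Joint power, 40 / 50 |
|---|---|---|
| 0 (plan) | 0.919 / 0.976 | 0.72 / 0.85 |
| 1% | 0.817 / 0.904 | 0.64 / 0.79 |
| 2% | 0.711 / 0.811 | 0.56 / 0.71 |
| 5% | 0.425 / 0.511 | 0.33 / 0.45 |

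(Exact Z-test times t-test, endpoints independent, true pain difference 0.)

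**5. Effect of single 2 mL events.** By the plan's criterion (unpooled lower bound above 0), one 2 mL event requires at least 6 events in the 5 mL arm: probability 0.68 at 40 per group and 0.86 at 50. Two events require at least 8: 0.35 and 0.61.

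**The case against.** The strongest defence is that 40 per group is a floor. The plan enrols 50 per group and calls its 20% loss conservative. Both co-primaries are measured during the PACU stay, so loss may well be small. At 50 evaluable and a 2 mL rate of 0, exact joint power is 0.85. This stands, and it means that a reader who infers that the trial's power simply is 33% to 72% goes too far. That range holds only at 40 evaluable per group with independent endpoints, and its lower end needs a 2 mL rate of 5%, which the protocol nowhere gives. The defence does not rescue the claim that power is kept after 20% loss, because that claim concerns the floor itself. Multiple imputation keeps patients in the analysis set but does not restore the lost information.

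A reader might also infer that one or two HDP events in the 2 mL arm would sink the trial. Step 5 shows otherwise: after one event, HDP superiority remains more likely than not. Only two events at 40 per group make failure the likelier result.

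Nor is the arithmetic behind 40 materially wrong. Taking 40.14 as 40 gives a power of 0.798 instead of 0.800. The pooled/unpooled mismatch is real but amounts to two patients per group, and enrolling 50 absorbs both.

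Finally, the 1e-20 is disclosed as a software workaround for a stated hypothesis. That is fair. What remains is that 0/11 cannot support a rate so close to 0 as the only case considered.

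**Conclusion.** The point holds in this form: 80% is the power for each endpoint, and the design does not have 80% power for its own success rule at the 40 evaluable per group on which it is sized. On the protocol's inputs joint power there is 0.64 (printed formulas) or 0.72 (exact) under independence, with a ceiling of about 0.79 under any correlation. At 50 evaluable it is 0.78 or 0.85, so with full retention and a 2 mL rate of 0 the exact calculation gives more than 80%. On that calculation, a true 2 mL rate of 1% already brings joint power at 50 to just under 80%, and higher rates lower it quickly.

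All figures take the SD of 1.6 and the 16.67% rate as given and assume no true pain difference. A true difference against 2 mL would reduce power further: at 0.2 points (assumed), pain-score power at 40 per group is 0.60. The fault lies in how power is stated and in the single best-case rate. The formula mismatch and the rounding are minor.

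**What to change.** Keep N=100 and revise the text.

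1. In Sample size calculation and Final sample size determination, state that 80% is the power for each endpoint.
2. In place of the single 1e-20 case, report joint power at 40 and 50 evaluable per group for 2 mL HDP rates of 0, 1, 2 and 5%, labelled as assumptions. State the method and the independence assumption.
3. In Handling of study withdrawals, qualify the statement about power. After 20% loss it holds per endpoint, to within rounding, and not for success on both.
4. Relabel the HDP formula as unpooled (39.2, so 40), or give the pooled figure (42). Round the pain-score figure up to 41.

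The cost is a rewritten sample-size section and a less favourable stated power. No patients are added, and the endpoints, tests and decision rule do not change.

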#### Statistical analysis

All statistical analyses will be performed in strict accordance with the pre-specified statistical analysis plan (SAP) finalized before database locking. The statistical software used will be IBM SPSS Statistics 25.0.01 (IBM Corp., Armonk, NY, USA). A two-tailed *p* value < 0.05 will be considered statistically significant, except for the one-sided tests specified for the non-inferiority and superiority primary endpoints.

##### Definition of analysis populations

Three distinct analysis populations will be defined and used for different analytical purposes:

(1) Intention-to-Treat (ITT) population (primary analysis population)

The ITT population includes all randomized subjects who have received at least one dose of the study intervention (2 mL or 5 mL 0.375% ropivacaine). This population will be used for the primary analyses of both co-primary endpoints (analgesic efficacy non-inferiority and HDP incidence superiority), as it preserves the randomization-generated group balance and minimizes selection bias, providing the most conservative and generalizable results.

(2) Per-Protocol (PP) population (sensitivity analysis population)

The PP population includes subjects who strictly adhere to the study protocol and meet all of the following criteria:

Received the full assigned study intervention with no wrong-group medication administrationCompleted all primary outcome assessments (pre-rescue NRS pain score and diaphragmatic excursion measurement in the PACU)Had no major protocol violations that could impact the interpretation of primary outcomes, including:

Preoperative use of prohibited analgesic or sedative medicationsUnplanned additional local anesthetic administration during the procedureIncomplete blinding due to accidental disclosure of group allocationLoss to follow-up before completion of primary outcome assessments

The PP population will be used for sensitivity analyses to verify the robustness of the ITT results. If the ITT and PP analyses yield consistent conclusions, the primary findings will be considered robust.

3 Safety analysis population.

The safety analysis population includes all randomized subjects who have received at least one dose of the study intervention. This population will be used for all safety-related analyses, including the incidence of adverse events and serious adverse events.

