**Methods and analysis:**

This is a prospective, single-center, randomized, non-inferiority trial conducted at Ningbo No.6 Hospital, China. A total of 100 patients undergoing elective arthroscopic shoulder surgery will be randomized in a 1:1 ratio to receive either 2 mL or 5 mL of 0.375% ropivacaine via ultrasound-guided subparaneural injection at the upper trunk bifurcation. The dual co-primary endpoints are the pre-rescue Numerical Rating Scale (NRS) pain score immediately after full consciousness in the post-anesthesia care unit (PACU) (non-inferiority margin = 1 point) and the incidence of ipsilateral HDP assessed before PACU discharge. Secondary outcomes include diaphragmatic function parameters, pulmonary function, perioperative analgesic consumption, recovery indicators, and adverse events. All statistical analyses will be performed according to the pre-specified statistical analysis plan, with the intention-to-treat population as the primary analysis set.

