##### Analysis of primary outcomes

(1) Non-inferiority analysis of analgesic efficacy (pre-rescue NRS pain score)

The primary non-inferiority endpoint is the difference in pre-rescue NRS pain scores between the 2 mL group and the 5 mL group immediately after full consciousness in the PACU. The mean difference (MD) and its one-sided 97.5% confidence interval (CI) will be calculated using the two-sample t-test for independent samples, assuming equal variances.

*Non-inferiority judgment criterion*: The 2 mL regimen will be considered non-inferior to the 5 mL regimen in terms of analgesic efficacy if the upper bound of the one-sided 97.5% CI for the mean difference (2 mL group minus 5 mL group) is less than the predefined non-inferiority margin of 1 point.

(2) Superiority analysis of diaphragmatic safety (HDP incidence)

The primary superiority endpoint is the difference in the incidence of ipsilateral HDP between the two groups. The risk difference (RD) and its one-sided 97.5% CI will be calculated using the two-sample Z-test for proportions.

*Superiority judgment criterion*: The 2 mL regimen will be considered superior to the 5 mL regimen in terms of diaphragmatic safety if the lower bound of the one-sided 97.5% CI for the risk difference (5 mL group minus 2 mL group) is greater than 0.

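### ITT is called most conservative for both co-primary endpoints, but that does not hold for NRS non-inferiority, and a failed per-protocol result cannot block the claim

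*Protocol article*

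**What the plan says.** Under Definition of analysis populations, the article says of the ITT set: "This population will be used for the primary analyses of both co-primary endpoints (analgesic efficacy non-inferiority and HDP incidence superiority"). The reasons follow in the same sentence: "as it preserves the randomization-generated group balance and minimizes selection bias, providing the most conservative and generalizable results". The abstract agrees, "with the intention-to-treat population as the primary analysis set", and Unblinding procedures also names ITT as the primary population.

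PP has a supporting role: "The PP population will be used for sensitivity analyses to verify the robustness of the ITT results". The only rule linking the two sets covers agreement: "If the ITT and PP analyses yield consistent conclusions, the primary findings will be considered robust". Sensitivity analyses repeats that both co-primary endpoints will be re-analysed in PP. Neither section says what follows if PP misses the margin.

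Analysis of primary outcomes sets the test: "The mean difference (MD) and its one-sided 97.5% confidence interval (CI) will be calculated using the two-sample t-test for independent samples". Non-inferiority is declared if the upper bound for 2 mL minus 5 mL "is less than the predefined non-inferiority margin of 1 point". That criterion does not mention PP. Multiplicity adjustment requires success on both endpoints, not in both populations.

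**The concern.** One justification is applied to two tests on which dilution acts in opposite directions.

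- **HDP superiority.** If some patients receive the other arm's volume, the risk difference shrinks towards 0 and superiority is harder to show. Here ITT is the cautious choice.
- **NRS non-inferiority.** The same errors shrink the 2 mL minus 5 mL difference towards 0. If 2 mL is truly worse, the upper bound moves down, towards the claim.

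The PP definition itself treats wrong-group medication as a reason for exclusion, so those patients remain only in the analysis that decides. The trial could therefore declare non-inferior analgesia on ITT while the PP bound lies above 1 point, and under the stated rule the claim would stand.

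**Working it through.** **Inputs from the protocol article.** Margin 1 NRS point; SD 1.6; one-sided alpha 0.025; power 0.80; 40 per group required; 50 per group recruited after a 20% dropout allowance.

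**Assumption.** The share q of each arm that receives the other volume is not given. A range of 0% to 10% is shown.

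**Step 1: the plan's own figure.** n = 2 × (1.96 + 0.84)² × 1.6² / 1² = 2 × 7.84 × 2.56 = 40.14, stated as 40 per group. Allowing for 20% dropout, 40 / 0.80 = 50 per group, 100 in total. The sample size reproduces and is not in question here.

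**Step 2: standard error.** With 50 per arm, SE = 1.6 × √(2/50) = 0.32.

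**Step 3: dilution.** Let the true difference equal the margin, 1.0, so that a non-inferiority claim is false. If a share q of each arm receives the other volume and responds accordingly, the expected ITT difference is (1 − 2q) × 1.0, a bias of 2q towards the claim.

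**Step 4: false non-inferiority.** Error ≈ Φ(−1.96 + 2q/0.32).

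| q in each arm | Expected ITT difference | Argument of Φ | One-sided error |
|---|---|---|---|
| 0% | 1.00 | −1.96 | 2.5% |
| 2% (1 patient per arm) | 0.96 | −1.96 + 0.125 = −1.835 | 3.3% |
| 5% | 0.90 | −1.96 + 0.3125 = −1.648 | 5.0% |
| 10% (5 patients per arm) | 0.80 | −1.96 + 0.625 = −1.335 | 9.1% |

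**Step 5: simulation.** The planned pooled t-test was simulated with 100,000 runs and 50 per arm. ITT alone gave 2.5% at q = 0, 4.2% at q = 4% in each arm and 8.5% at q = 10% in each arm. The last figure is slightly below the approximation, which ignores the wider observed SD in mixed arms. When the bound had to be below 1 point in both ITT and PP, the error was 2.4% to 2.5% throughout. These runs take the violations to be unrelated to outcome.

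**Step 6: power at a true difference of 0.** With 50 per arm, Φ(1/0.32 − 1.96) = Φ(1.165) = 88%. With 40 per arm, SE = 1.6 × √(2/40) = 0.358 and Φ(1/0.358 − 1.96) = 80%. The design target is "and a statistical power (1-*β*) of 0.80".

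**The case against.** **Wrong-volume errors should be rare.** Each patient gets one injection. One dedicated nurse prepares it from a numbered envelope opened just before the block and logged, and the operator knows the volume. Rates of 5% to 10% in each arm would mean about 5 to 10 of 100 patients receiving the other volume. This stands: the low rows of the table are the realistic ones, and with near-perfect adherence the effect is negligible.

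**Conservatism is not the only reason given.** The same sentence cites preserved randomization balance and reduced selection bias, both sound reasons for ITT in a non-inferiority trial. This stands too. The fault lies in the added claim of conservatism for the NRS endpoint, not in using ITT.

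**PP is not ignored.** Its re-analysis is pre-specified, and a discordant PP result could not be called robust under the protocol's own sentence. A SAP that is not shown might say more. But the article states its decision criterion in full, and that criterion lets the claim stand whatever PP shows.

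**PP is not clean either.** It excludes on post-randomization events, including accidental disclosure of allocation and missing primary outcomes. It can be biased in either direction, and not every exclusion concerns a violation that dilutes. That argues for requiring both sets rather than replacing ITT with PP.

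**A stronger reading is tempting.** A reader might infer that a weak 2 mL block would prompt extra anesthetic or analgesic that lowers the 2 mL scores within ITT. The documents do not support this pathway. The listed analgesic and sedative violations are preoperative, so they precede any sign of a weak block. The block section forbids local anesthetic beyond the assigned volume and describes no adequacy test that would prompt more. The NRS is taken before PACU rescue. Intraoperative sufentanil is allowed by the anesthesia protocol, so its use is no violation, it stays in PP as well, and a two-set rule would not remove it.

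**Conclusion.** The concern holds in a limited form. Calling ITT most conservative is right for HDP superiority and not generally right for NRS non-inferiority. As the criterion is written, a PP failure cannot block the claim.

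The size depends on a violation rate the protocol does not give. A single wrong-volume case in each arm raises the false non-inferiority rate from 2.5% to about 3.3%. It takes 5% in each arm to reach about 5%, and 10% to reach 8.5–9%. These figures assume a true difference at the margin, SD 1.6, 50 per arm and patients who respond according to the volume received. The documents do not show that the higher rates are likely, so this is a flaw in the stated rationale and decision rule, not evidence that a substantial bias will occur.

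**What to change.** Under Definition of analysis populations, limit the conservatism argument to the HDP superiority endpoint; the other two reasons for ITT can stay for both.

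Under Analysis of primary outcomes, state that NRS non-inferiority will be declared only if the upper bound of the one-sided 97.5% CI for 2 mL minus 5 mL is below 1 point in both the ITT and the PP population. Keep ITT alone as the deciding set for HDP.

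This changes wording only, because the PP analysis is already planned. The cost is some power for the NRS endpoint if PP is smaller than ITT. Success in both sets cannot be more likely than success in PP alone, which is about 88% if all 50 per arm remain and about 80% if 40 do, close to the design target.
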